## Abstract

**Introduction:**

Orofacial pain and tension headache are symptoms that affect a large portion of the population, compromising productivity, social ability, and functional development. The treatment for reducing painful sensation should be chosen carefully, as pharmacological treatment may bring side effects and overload the organism of patients in pain. Low-level laser therapy has been used with local and systemic [vascular] applications for pain control. However, there is still uncertainty in the literature about the ideal dosimetric parameters for photobiomodulation treatment according to patient characteristics.

**Methods:**

The objective of this project is to validate a dosimetry model based on the relationship between the effects of photobiomodulation with anthropometric and hemodynamic variables, both in local application and systemic application in patients with symptoms of orofacial pain and tension headache. For this purpose, 180 participants with orofacial pain post-covid eligible participants will be randomly assigned to Group 1—Local Photobiomodulation, Group 2—Vascular Photobiomodulation, Group 3—Placebo Local Photobiomodulation, or Group 4—Placebo Vascular Photobiomodulation [Therapy EC–DMC device, São Carlos, Brazil,– 660 nm, 100mW] using stratified block randomization. Before the application, sociodemographic information such as age, skin phototype [classified by the Fitzpatrick scale], weight, height, body mass index [BMI], oxygen saturation [SaO2], blood pressure [BP], heart rate [HR], and thickness of skin, fat, and facial muscles will be collected. During the application, we will collect local temperature, SaO2, BP, and HR. Before and after laser application, blood levels of lactate and hemoglobin, BP, and HR will be measured in the first and last session. In addition to demographic, anthropometric, and hemodynamic variables, the penetrated energy will be quantified using a power meter, and information from orofacial pain and headache symptom questionnaires will be analyzed. The Monte Carlo simulation technique will be used to systematically study the relationship between the light penetration profile into the target tissues and the most relevant variables, namely BMI, tissue layer thicknesses, and skin phototype. Light transmittance, measured in vivo and simulated, will be compared to validate a personalized dosimetry model.

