In another systematic review published in 2022 [10], the objective was to determine which dosimetric parameters of photobiomodulation provide better effects in reducing pain in patients with orofacial pain. The authors observed that the parameters of wavelength, energy, time, and irradiance were quite different among the included clinical trials. The use of diode or gallium-aluminum-arsenide [GaAlAs] lasers, with wavelengths ranging from 400–800 nm or 800–1500 nm, and energy densities below 25 J/cm^2^ has been documented [10]. For patients with joint pain, diode laser and wavelength between 400 and 800 nm were used. For patients with muscular pain, the following lasers and parameters were used: diode laser, wavelength between 800 and 1500 nm, and 25 J/cm2. For patients with joint and muscular pain, infrared laser, wavelength of 800–1500 nm, 100 J/cm2, and an application time between 15 and 30 s or >60 seconds.

Following this line of research, a clinical trial was conducted to assess the cost-effectiveness of laser therapy in managing facial pain. The research demonstrated that photobiomodulation presented analgesic effects and proved to be more cost-effective compared to placebo and occlusal splint [12].

Clinical trials assessing the effectiveness of photobiomodulation have yielded different conclusions regarding dosimetry, and there remains an uncertainty regarding the development of protocols, considering dosimetric parameters and the justification for choosing such parameters in published works [9].

The delivery of energy during photobiomodulation therapy requires the transmission of photons through outer tissue layers, such as skin and fat, before reaching the desired target. We believe that the thickness of these layers in patients with different body compositions may interfere with the expected results of therapy. However, these data have not yet been explored in clinical trials on this topic [10].

Based on the need for greater dosimetric precision according to individual characteristics, we hypothesize that anthropometric and hemodynamic variables can be used to determine the appropriate parameters for delivering energy as close to the ideal as possible in controlling orofacial pain [12].

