#### Monte Carlo simulation

The Monte Carlo technique will be employed to simulate the fluence profile, energy deposited in different tissue layers of the cheek and index finger, and transmittance, using light of wavelengths 660 nm and 808 nm. In an initial phase, a Monte Carlo model will be developed, considering the morphological structure of the tissues to be treated, approximating their structure to a planar and laminar model consisting of four layers: epidermis, dermis, subcutaneous fat, and muscle [15].

The thicknesses of each layer will be obtained from the literature, and their values will be varied in predefined intervals consistent with literature findings for different age groups and BMI values. The optical properties of each layer, including absorption and scattering coefficients, anisotropy coefficient, and refractive index, will be gathered from bibliographic research, considering the expected variability for the sample under study.

A model for the absorption coefficient will be used, accounting for blood content in each layer, blood oxygen saturation level, as well as fractions of fat, melanin, and water in each tissue layer. Based on the preliminary study, a database will be established aiming to establish a relationship between energy deposited in tissues and different anthropometric characteristics [13, 16].

Special attention will be given to the relationship between energy deposited in the epidermis and muscle, to establish a compromise between safety limits and treatment effectiveness. Simulated transmittance values will be subsequently compared with values measured in volunteers, considering measurements of tissue thickness by ultrasound, skin type, BMI, and blood saturation levels. A computational implementation of the tissue optical model and the Monte Carlo simulation model will be developed based on Marti et al.’s MCMatlab code, available online [https://github.com/ankrh/MCmatlab], using Matlab® software, version 2022.

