### Expected results

It is expected that we will ascertain whether there is a difference between the effects of vascular and local photobiomodulation on orofacial pain, with the study’s aim to develop and validate a dosimetric model for individualized protocols based on the unique characteristics of each patient.

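### The simulated-versus-measured comparison that is to validate the personalized dosimetry model does not separate accuracy on average from prediction of the individual

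*Protocol article*

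**What the plan says.** The hypothesis in the Introduction concerns individuals: "we hypothesize that anthropometric and hemodynamic variables can be used to determine the appropriate parameters". Expected results gives the aim as to "develop and validate a dosimetric model for individualized protocols based on the unique characteristics of each patient".

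The validation step appears twice. The Abstract (Methods) says: "Light transmittance, measured in vivo and simulated, will be compared to validate a personalized dosimetry model". The Monte Carlo simulation section says: "Simulated transmittance values will be subsequently compared with values measured in volunteers", and adds that this is done "considering measurements of tissue thickness by ultrasound, skin type, BMI, and blood saturation levels". How those individual measurements enter is not described.

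In the initial phase the inputs are not the participants' own. On thickness: "The thicknesses of each layer will be obtained from the literature, and their values will be varied in predefined intervals". Optical properties likewise come from published sources.

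The Light transmission section names two measurement sites, the index finger and the cheek. The simulation covers 660 nm and 808 nm. No section describes a run of the same model at average inputs against which the individualized run could be judged.

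**The concern.** To call a dosimetry model personalized is to claim a contrast: using a participant's own tissue thickness, phototype, BMI and saturation predicts light transmission better than using typical values for everyone. The stated comparison has two terms, simulated and measured transmittance. Agreement between them can arise from three sources: the right overall level, the right difference between cheek and finger, or the right ranking and spread of individuals within a site. Only the third supports personalization, and the comparison as described does not separate it from the other two.

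At stake is the main conclusion. A simulation that reproduces average transmittance is useful, but it does not justify setting energy by individual characteristics. If the individual inputs add nothing, or add error, a dosimetry tool built on them would be less accurate than one fixed setting of the same model.

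**Working it through.** The article gives no agreement statistic, acceptance limit or sample-size calculation for the validation, so there is no figure to reproduce. The check asks which common forms of comparison would detect a model without individual predictive value.

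**Inputs from the article.** Total sample 180 (Sample); 1:1:1:1 allocation (Randomization), so 180/4 = 45 per group; two measurement sites (Light transmission); no laser light in the two placebo groups (Groups 3 and 4). Treatment-time transmittance is therefore available for at most 2 × 45 = 90 participants, and for 45 per active modality.

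**Assumptions, none given in the article.** Log transmittance is scaled so that its between-person SD within a site is 1. The simulated values have the correct site mean, SD s, and within-site correlation ρ with the measured values. The fixed-input run returns the site mean for everyone.

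**Error relative to the fixed-input run.** MSE(fixed) = 1 and MSE(individual) = 1 + s² − 2ρs. Hence

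skill = 1 − MSE(individual)/MSE(fixed) = 2ρs − s².

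- No individual signal (ρ = 0): skill = −0.06, −0.25 and −1.00 for s = 0.25, 0.5 and 1.
- Informative and well scaled (ρ = 0.5, s = 0.5): 0.50 − 0.25 = +0.25.
- Informative but over-spread (ρ = 0.4, s = 1): 0.80 − 1.00 = −0.20.

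Individual inputs raise the error whenever s exceeds 2ρ, even though the correlation is positive.

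**How often a model with ρ = 0 looks acceptable** (simulation, s = 0.6 unless stated):

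| Form of comparison | 45 per site | 180 per site |
|---|---|---|
| Paired mean test, no significant difference | 95% | 95% |
| Correlation pooled over cheek and finger, positive and significant; site gap 0.5 / 1 / 2 SD | 14% / 81% / 100% | 43% / 100% / 100% |
| Within-site, per-person correlation, positive and significant | 2–3% | 2–3% |
| Lower squared error than fixed-input run, one-sided 2.5% | <0.1% | <0.1% |

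The pooled result has a closed form. With equal numbers per site and gap D, the between-site variance is D²/4, so r = (D²/4)/√[(1 + D²/4)(s² + D²/4)]. For D = 3 and s = 1 this is 2.25/3.25 = 0.69; for s = 0.25 it is 2.25/√(3.25 × 2.3125) = 0.82. Neither contains any within-site prediction.

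Limits of agreement would be ±1.96√(1 + s²), that is ±2.02 to ±2.77 for s from 0.25 to 1, against ±1.96 for a constant prediction. They reveal the problem only when set beside that constant-prediction reference.

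**What a within-site correlation misses.** For the over-spread model (ρ = 0.4, s = 1, 45 participants), the within-site correlation is positive and significant in about 79% of replicates, yet the individualized run has larger error than the average-input run in about 77%.

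**Precision of the error comparison.** With ideal scaling (s = ρ), a one-sided 2.5% test of lower error has power of about 26%, 43% and 62% at 45 participants for ρ = 0.4, 0.5 and 0.6, and 81%, 97% and over 99% at 180.

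**The case against.** A reader might infer that a model with no individual signal passes this trial's validation. The article does not support that. It says only that the values will be compared, and it fixes no metric, pooling choice or pass rule. Those details may stand in a full protocol or analysis plan that is not shown, so their absence is not itself a fault. The Monte Carlo simulation section also points towards a participant-level comparison, since ultrasound thickness, skin type, BMI and saturation are to be taken into account. If that is analysed per person within each site, a model with no signal would be exposed nearly every time. The 95% and the 14% to 100% figures belong to mean-level and site-pooled readings that the article does not propose, and the pooled figures depend strongly on an assumed site gap.

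It is also fair to say that reproducing the average is a real test, because the optical properties come from the literature and are not fitted to this sample. Transmittance need not be linear in thickness, so the output at average inputs need not equal the average output.

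All of this stands and limits the point to what could happen. The narrower criticism remains: the article names the comparison that is to validate personalization, and that comparison lacks the contrast the claim needs. Taking individual values into account does not show that they help, and the within-site correlation that rescues the first case does not catch inputs that enlarge the error.

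**Conclusion.** The point holds in limited form. Simulated-versus-measured agreement, as described, does not distinguish a model that is right on average from one that predicts individuals. Under a mean-level or site-pooled analysis, a model with no individual value could be called validated. Under a within-site, per-person correlation that would happen only about 2–3% of the time, but a model whose individual inputs worsen prediction could still look successful (about 79% significant, about 77% with larger error, in the example above).

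These sizes rest on assumed spreads, site gaps and correct site means, and they illustrate the mechanism without forecasting this trial. The 180-participant figures are optimistic if transmittance is read only during active treatment. The Light transmission section says each participant, but the cheek reading is taken while the laser is applied and the placebo devices emit no light, so 45 to 90 is more likely unless a separate reading is made.

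**What to change.** In the Monte Carlo simulation section, with a matching phrase in the Abstract, state that for every participant with measured transmittance the same code will be run twice: once with that participant's own thickness, phototype, BMI and saturation, and once with fixed average inputs. Separately for each site and wavelength, report the within-site association of simulated with measured values, and the difference between the two runs in squared prediction error of log transmittance, with a confidence interval. Do not pool sites or wavelengths for this purpose.

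Describe the model as validated for personalization only to the extent that individual inputs lower the error. Otherwise limit the conclusion to how well the simulation reproduces average transmittance, judged from its own mean bias, because failing to lower the error does not show that the mean is right. A hard significance threshold on the error difference is not recommended: with 45 participants it would often withhold the claim from a model that does predict individuals.

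The cost is one extra set of simulation runs and a few sentences, with no new participants or measurements. The drawback is a possibly weaker claim, because the interval will be wide if only 45 to 90 participants contribute.

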**Discussion:**

The results of this study contribute to validating a Monte Carlo Simulation model to calculate the appropriate dosimetry for photobiomodulation therapies in the control of patients with Post-Covid-19 orofacial pain.

**Trial registration:**

**Trial registration number**: NCT06065969.

## Introduction

Orofacial pain has been classified according to its location as dental, periodontal, osseous, muscular, neural, in oral mucosa, in salivary glands, and in the temporomandibular joint [1, 2]. It may also present similar manifestations to primary headaches, be of idiopathic origin, or be associated with psychological [anxiety, catastrophizing, and depression] and social factors [access to medical care, stigmas, and support from family and friends] [3, 4]. Pain of dentoalveolar origin and associated structures is the most common complaint in the orofacial region [5, 6] with non-odontogenic pain originating from temporomandibular disorder [TMD] being the most diagnosed in this region [3, 7].

The treatment plan for orofacial pains should be tailored to the individual’s needs. Different therapies can assist in reducing the painful sensation in this context. Caution is advised in the choice of invasive therapies and irreversible treatments as first-line therapies [8, 9].

Occlusal splints, ultrasound, manual physiotherapy, drug therapy, transcutaneous electrical oral stimulation, and photobiomodulation [PBM], they are among the non-invasive treatments that have been used to alleviate orofacial painful conditions [10]. Low-level laser therapy, as a form of photobiomodulation, has been used as an alternative treatment due to its non-invasive and safe nature, related to its characteristics of low-intensity energy and wavelength, and its presentation of anti-inflammatory, analgesic, and other therapeutic biological responses [11]. The mechanism of PBM may be associated with its influence on the synthesis, release, and metabolism of various substances related to pain and analgesia [9].

In the systematic review and meta-analysis [11] out of 85 articles published between 2009 and 2020, 8 randomized clinical trials were evaluated, comparing photobiomodulation treatment with the placebo group in 181 participants with myofascial orofacial pain. The results were satisfactory for controlling painful sensations; however, the authors highlighted the significant variability in equipment and dosimetric parameters. The difference in the choice of energy, power, and wavelength among the included studies does not allow for the development of an ideal dosimetric protocol for treatment.

In another systematic review published in 2022 [10], the objective was to determine which dosimetric parameters of photobiomodulation provide better effects in reducing pain in patients with orofacial pain. The authors observed that the parameters of wavelength, energy, time, and irradiance were quite different among the included clinical trials. The use of diode or gallium-aluminum-arsenide [GaAlAs] lasers, with wavelengths ranging from 400–800 nm or 800–1500 nm, and energy densities below 25 J/cm^2^ has been documented [10]. For patients with joint pain, diode laser and wavelength between 400 and 800 nm were used. For patients with muscular pain, the following lasers and parameters were used: diode laser, wavelength between 800 and 1500 nm, and 25 J/cm2. For patients with joint and muscular pain, infrared laser, wavelength of 800–1500 nm, 100 J/cm2, and an application time between 15 and 30 s or >60 seconds.

Following this line of research, a clinical trial was conducted to assess the cost-effectiveness of laser therapy in managing facial pain. The research demonstrated that photobiomodulation presented analgesic effects and proved to be more cost-effective compared to placebo and occlusal splint [12].

Clinical trials assessing the effectiveness of photobiomodulation have yielded different conclusions regarding dosimetry, and there remains an uncertainty regarding the development of protocols, considering dosimetric parameters and the justification for choosing such parameters in published works [9].

The delivery of energy during photobiomodulation therapy requires the transmission of photons through outer tissue layers, such as skin and fat, before reaching the desired target. We believe that the thickness of these layers in patients with different body compositions may interfere with the expected results of therapy. However, these data have not yet been explored in clinical trials on this topic [10].

Based on the need for greater dosimetric precision according to individual characteristics, we hypothesize that anthropometric and hemodynamic variables can be used to determine the appropriate parameters for delivering energy as close to the ideal as possible in controlling orofacial pain [12].

Therefore, the aim of this project is to evaluate a Monte Carlo simulation model to predict the distribution of energy and its effects related to anthropometric and hemodynamic variables in photobiomodulation treatment with both local and systemic applications across different age groups [13].

With the development of this study, we expect to create and validate a Monte Carlo Simulation model to calculate the appropriate dosimetry for photobiomodulation therapies in orofacial pain control, according to the physical and physiopathological characteristics of each person. In this way, healthcare professionals can deliver energy closest to the ideal in treatment, achieving desired results, reducing unnecessary exposure time, and avoiding under or over-treatment.

## Materials and methods

### Study location, sample selection, and ethical considerations

This is a clinical study for the validation of a dosimetric model. It received approval from the Research Ethics Committee of Nove de Julho University with protocol number 6.080.655 S2 File. For participants under the age of majority, an assent form will be prepared, along with a consent form for their respective guardians (S1 File). The clinical procedures for recruitment, eligibility assessment, and methodological processes will be conducted at the Integrated Health Outpatient Clinics of UNINOVE–Vergueiro Unit São Paulo, SP, Brazil. Monte Carlo Simulation modeling techniques and statistical analyses will be performed in collaboration with the Department of Physics at the University of Beira Interior Covilhã, Portugal. This study was drafted and planned in accordance with the recommendations outlined in the SPIRIT Standard Protocol Items for Randomized Trials–S3 File statement. The participants will sign a statement of informed consent agreeing to participate in the study. Clinical trial registry: ClinicalTrials.gov Identifier: NCT06065969.

### Sample

Individuals between 7 and 19 years of age with orofacial pain post-covid-19 will be invited to participate in the study. A convenience sample was chosen, totaling 180. Given the lack of definitive studies for sample size calculation regarding persistent COVID-19 symptoms, a convenience sample was used. Participants were chosen based on reported symptoms and inclusion criteria at the university outpatient clinic. This approach was necessary due to the evolving nature of post-COVID-19 symptomatology, which currently prevents standardized sample size determination.

### Inclusion criteria

Individuals at least 1 symptom of pain and/or headache, according to the American Academy of Orofacial Pain (AAOP)questionnaire and the headache questionnaire based on the International Classification of Headache Disorders, 3^rd^ edition (ICHD-3) [14].

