### Study variables

Sociodemographic information such as age, skin phototype [classified by the Fitzpatrick scale], weight and height. The primary outcome is orofacial pain, and the secondary outcomes are oxygen saturation, blood pressure, heart rate, local temperature, blood lactate levels, and hemoglobin levels. In addition to demographic, anthropometric, and hemodynamic variables, the penetrated energy will be quantified using a power meter, and information from orofacial pain and headache symptom questionnaires will be analyzed.

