### Randomization

The participants will be informed that they will be randomly assigned to one of the four study groups that will be compared. To allocate the participants to the groups, a stratification process will be carried out based on the answers to the questionnaires and the presence of orofacial pain symptoms and the presence of headache symptoms will be considered strata. Stratification will be carried out to balance the allocation of participants in each group according to stratum.

After stratification, participants will be randomized in a 1:1:1:1 ratio into the 4 groups. The randomization list will be generated by an independent researcher in random blocks of four, electronically via the ramdomizer.org website and kept in opaque envelopes. The allocation will only be revealed to the operating researcher at the time of the intervention. A study team member, separate from the researcher who will administer the intervention, will follow the random allocation sequence to assign participants to a study group and prepare study equipment and materials. Eligible participants will be randomly assigned to Group 1—Local Photobiomodulation, Group 2—Vascular Photobiomodulation, Group 3—Placebo Local Photobiomodulation, or Group 4—Placebo Vascular Photobiomodulation using stratified block randomization generated by the study statistician.

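### The protocol article is inconsistent on whether headache alone qualifies for entry; if it does, the treatment effect on orofacial pain, the only primary outcome, shrinks by the headache-only share

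*Protocol article*

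**What the plan says.** Four places in the protocol article bear on who is enrolled and what is measured.

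- **Abstract (Methods) and Sample.** The Abstract has "180 participants with orofacial pain post-covid eligible participants will be randomly assigned". Sample says "Individuals between 7 and 19 years of age with orofacial pain post-covid-19 will be invited to participate in the study". Both describe people who have orofacial pain.
- **Inclusion criteria.** The one listed criterion is "Individuals at least 1 symptom of pain and/or headache", judged on the AAOP questionnaire together with a headache questionnaire based on ICHD-3. One headache symptom and no orofacial pain meets it.
- **Randomization.** Allocation is stratified: "the presence of orofacial pain symptoms and the presence of headache symptoms will be considered strata". The ratio is 1:1:1:1.
- **Study variables.** "The primary outcome is orofacial pain, and the secondary outcomes are oxygen saturation, blood pressure, heart rate", followed by temperature, lactate and hemoglobin. Headache is not a listed outcome, although the section says that the headache questionnaire data will be analysed.

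On size, Sample says "A convenience sample was chosen, totaling 180" and gives no power calculation.

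**The concern.** A participant who enters with headache and no orofacial pain starts the primary outcome with nothing to improve. Stratified randomisation spreads such participants evenly over the four arms, so it protects the comparison from imbalance. It does not stop them from pulling the active-minus-sham difference towards zero.

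At stake is the comparison of arms on pain. A diluted estimate describes a mixture of two symptom groups in unknown proportion, and a null result could mean either no effect or many participants who could not respond. Because the sample size is a convenience figure, there is no stated margin to absorb the loss.

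**Working it through.** **Step 1: the sections side by side.** Read alone, Sample and the Abstract imply that everyone has orofacial pain. Read alone, Inclusion criteria implies that some need not. Randomization supports the second reading: if everyone had orofacial pain, its presence would be a constant and could not serve as a stratification factor. Neither reading satisfies all the sections, so the document is inconsistent on this point.

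**Step 2: arm size.** 180 / 4 = 45 per arm. The total of 180 has no inputs behind it and cannot be reproduced further.

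**Step 3: dilution.** Let f be the headache-only share in each arm, and δ the active-minus-sham difference in mean improvement among those with orofacial pain. Headache-only participants have mean change 0 in both arms, so

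difference in all randomised = (1 − f) × δ + f × 0 = (1 − f) × δ.

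The article gives neither f nor δ. Assume δ = 0.60 SD. This is close to the effect that 45 per arm detects with 80% power at two-sided 5% (also assumed): (1.96 + 0.84) × √(2/45) ≈ 0.59 SD. In whole participants per arm:

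| Headache-only per arm | With orofacial pain | Expected estimate, all randomised |
|---|---|---|
| 9 (20%) | 36 | 36/45 × 0.60 = 0.48 SD |
| 15 (33%) | 30 | 30/45 × 0.60 = 0.40 SD |
| 23 (51%, nearest above 50%) | 22 | 22/45 × 0.60 = 0.29 SD |

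**Step 4: power, all randomised against the restricted set.** Simulated two-sample comparison, 45 per arm. Participants with orofacial pain are drawn from N(0.6, 1) on active and N(0, 1) on sham. Headache-only participants are either constant at zero change, or vary around zero with SD 1.

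| f | All, constant zero | All, SD 1 | Restricted to baseline orofacial pain |
|---|---|---|---|
| 20% | 71% | 61% | 71% |
| 33% | 62% | 46% | 63% |
| 50% | 47% | 27% | 49% |

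Figures carry simulation error of about one percentage point. With f = 0, power is about 80%. The constant-zero column is the more favourable of the two for keeping everyone, and even there restriction loses nothing.

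**Step 5: cost of keeping everyone.** If the SD stays unchanged, holding 80% power at the 0.59 SD reference effect multiplies the arm size by 1/(1 − f)². At f = 20% this is 1/0.64 = 1.56, or 71 per arm; at f = 50% it is 4, or 180 per arm.

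**The case against.** The strongest reply is that Sample governs. It limits invitation to people with orofacial pain and says that participants are chosen on reported symptoms and the inclusion criteria, so the criterion can be read as operating inside that population. On that reading no headache-only participant is enrolled and there is no dilution. This stands as a possible reading, and it is why the point is a conflict to resolve. A reader might infer that part of each arm certainly cannot respond; the documents do not establish that. But the reply leaves the stratification on orofacial pain without a function, so the text would still need correcting.

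A second reply is that the analysis plan, which is not shown, may restrict the primary analysis to those with baseline orofacial pain. It may. That would remove the dilution, but it would not settle eligibility or stratification, which the protocol fixes, and fewer than 45 per arm would inform the primary question.

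Third, the stated aim is to validate a dosimetry model in patients with orofacial pain and tension headache. Comparing simulated with measured light transmittance does not depend on which symptom qualified the participant. This stands: the concern is confined to the comparison of arms on pain.

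Two further inferences are tempting but unsupported:

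- **Overlapping strata.** Someone with both symptoms might seem to belong to two lists. The text names two yes/no characteristics, which cross into mutually exclusive cells, and nothing describes separate lists.
- **No COVID-19 requirement.** The inclusion list does not repeat it, but the post-COVID condition is in Sample, in the same sentence as the age range, which the list does not repeat either.

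**Conclusion.** The point holds as an internal conflict with a conditional consequence. Sample and the Abstract describe an orofacial pain population; Inclusion criteria and Randomization allow for, and imply, participants without it; the only primary outcome is orofacial pain. If the inclusion criterion is applied as written, the expected treatment difference falls by the headache-only share: from 0.60 SD to about 0.48, 0.40 or 0.29 SD at shares of 20%, 33% or 50%.

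The direction of the dilution rests on one assumption, that participants with no orofacial pain at baseline show no mean difference between arms on it. The size rests on f and the 0.60 SD effect, neither of which is in the document. The power figures also depend on how variable the headache-only scores are, and the article gives no outcome scale from which to judge that.

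**What to change.** Reconcile Sample, Inclusion criteria and Randomization in one of two ways.

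1. **Narrow the criterion to match Sample.** Require at least one orofacial pain symptom at entry, with headache allowed in addition. Presence of orofacial pain then drops out as a stratification factor and presence of headache remains. The cost is slower recruitment.
2. **Keep headache-only entry and define the primary analysis accordingly.** Take as the primary analysis set all randomised participants with at least one orofacial pain symptom at baseline, adjusted for the crossed strata, and analyse headache-only participants for headache. Write out the cells: orofacial pain only, headache only, both. Because the set is defined by baseline data and by a stratification factor, the randomised comparison is preserved. The cost is a primary analysis with fewer than 45 per arm (36 at f = 20%, 30 at 33%), although power is about the same as in all randomised participants, or better.

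Both options change wording only and need no new data collection. Either should be settled before unblinding. Under option 2, the article should also state how many participants with baseline orofacial pain the total of 180 is expected to yield.
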